#### Sampling design

Sampling involves purposive sampling for recruitment and then random assigned to experimental and waitlist control groups in 1:1 ratio. To ensure allocation concealment, an independent researcher, unaffiliated with this study, will be responsible for generating the randomization sequence. This researcher will not be involved in participant recruitment, enrollment, or data collection. Randomization can be achieved using the research randomizer software [42]. Participants will be blinded to their group assignment throughout the study. Unblinding will only be permitted under exceptional circumstances and with prior approval from the research ethics committee.

The sample size for this study is determined to be 80 participants, considering an anticipated 25% dropout rate. This decision is informed by the considerations outlined in a similar randomized control trial (RCT) to study the efficacy of a skills training program for 58 mental health support providers by Perlman et al. [43]. The sample size of 60 participants will provide 80% power to detect an effect size of 0.8 [44] between the intervention group and the control group at 5% level of significance (two-tailed test) as evidenced in a similar study by Ho et al. [45] with 68 participants.

To explore contrasting perspectives and for an in-depth understanding of the participant’s experiences, focus groups will be chosen using a targeted homogeneity sampling method, aiming to include those with both the highest and lowest score variances on attitude and self-efficacy scales.

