#### Data analysis

Descriptive statistics will be provided for baseline (T1) data. Participant demographics (e.g., age, gender, profession, years of experience, setting) will be described using frequencies and measures of central tendency as appropriate. Internal consistency (e.g., Cronbach's alpha) of both BAT-Q and COSE-TR for Indian population will be evaluated using Jamovi 2.4 software. Missing data will be handled with multiple implementations. Normality of the data will be assessed using the Shapiro–Wilk test.

If the data is found to be normally distributed, independent samples t-test will be used to report the baseline characteristics of the intervention and control groups. ANCOVA will be used to compare the post-intervention outcomes (T2) (self-efficacy, values and attitudes) between the intervention and control groups while statistically controlling for baseline (T1) differences. If the ANCOVA reveals a significant group effect, post-hoc comparisons will be conducted to identify specific differences. Paired samples t-test will be used to analyze changes within each group from pre-test (T1) to post-test (T2) to assess whether there are significant changes over time within each group. If the data is not normally distributed, Templeton’s two-step approach for transformation will be applied. After transformations if the data fails to meet the normality assumption, Mann–Whitney U test will be used to report baseline characteristics. Kruskal–Wallis test can be to identify specific differences between groups. Wilcoxon Signed-Rank Test can be used to assess significant changes over time within each group. All changes will be reported for attitudes, values and four subdomains of self efficacy and p values below 0.05 will be considered significant. Jamovi software will be used for statistical analysis.

To understand the factors influencing the changes observed in the quantitative data, a qualitative analysis will be conducted using six step thematic analysis described Braun and Clarke [38]. Focus group recordings will be transcribed verbatim. The transcripts will be systematically coded, identifying recurring ideas, patterns, and significant quotes related to participants' experiences and explanations for their attitude and self-efficacy changes. Thematic comparisons will be drawn between participants who exhibited significant positive and negative changes in their attitudes, values, and self-efficacy.

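### The printed power does not follow from its inputs: by two-sample t-test, 60 analysed participants give about 86% power for an effect size of 0.8, not 80% (a minor, conservative error)

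*Protocol article*

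**What the plan says.** The justification is in the protocol article, Phase 3, Sampling design. Enrolment is given first: "The sample size for this study is determined to be 80 participants, considering an anticipated 25% dropout rate". The power statement follows: "The sample size of 60 participants will provide 80% power to detect an effect size of 0.8", "at 5% level of significance (two-tailed test"). Participants are "random assigned to experimental and waitlist control groups in 1:1 ratio", so 60 means 30 per arm.

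The section does not name the test behind the calculation or say in what metric the 0.8 is expressed. It refers to two earlier trials of similar programmes, with 58 and 68 participants, as having informed the choice.

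The Data analysis section of Phase 3 plans the between-group comparison as follows: "ANCOVA will be used to compare the post-intervention outcomes (T2) (self-efficacy, values and attitudes) between the intervention and control groups", adjusting for the baseline score. Rank-based tests enter only if normality still fails after transformation.

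**The concern.** Sample size, effect size, significance level and power are tied together: once three are fixed, the fourth follows. The protocol prints all four, together with the allocation ratio, so the statement can be checked without any outside source. Under the usual calculation for two means, it does not reproduce.

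What is at stake is modest. This sentence is the protocol's only numerical statement of what the trial can detect, and a reader of a null result will rely on it. On the printed figures, a true effect of 0.8 would be missed 20% of the time. On the protocol's own inputs it would be missed about 14% of the time. The Introduction also invites researchers in other countries to adapt this protocol, so the figure may be reused.

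**Working it through.** **Inputs (all from Sampling design)**

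- Analysed: 60, at 1:1, so n = 30 per arm.
- Effect size: 0.8, read here as a standardised mean difference d. This is an assumption, because the metric is not named.
- Significance level: 0.05, two-sided.
- Stated power: 80%.
- Dropout 25%, enrolment 80.

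**1. The dropout step reproduces.** 60/(1 − 0.25) = 80. So 60 is the number meant to be analysed, and dropout does not explain the mismatch.

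**2. Power at n = 30 per arm.** The noncentrality is d × √(n/2) = 0.8 × √15 = 3.098, with 58 degrees of freedom.

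- Noncentral t: power = 86.1%.
- Normal approximation: Φ(3.098 − 1.960) = Φ(1.138) = 87.3%.

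The stated figure is 80%.

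**3. Sample size for 80% power at d = 0.8.**

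- Noncentral t: 25.5 per arm before rounding. 25 per arm gives 79.1% and 26 per arm gives 80.7%, so 26 per arm, or 52 in total.
- Normal approximation: 2 × (1.960 + 0.842)²/0.8² = 24.5, so 25 per arm, or 50 in total.

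The stated figure is 60. Starting from 52, enrolment would be 52/0.75 = 69.3, so 70.

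**4. Effect detectable at 80% power with n = 30 per arm.**

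- Noncentral t: d = 0.736.
- Normal approximation: (1.960 + 0.842) × √(2/30) = 0.723.

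The stated figure is 0.8.

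**5. Could another reading return 80%?**

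| Reading | Power, 60 analysed, d = 0.8 | Fits the text? |
|---|---|---|
| One-sided 5% | 92.2% | No: two-tailed is stated |
| 2:1 allocation | 81.9% | No: 1:1 is stated |
| Two-sided 2.5% | 78.5% | No: 5% is stated |
| Rank test, efficiency 0.955 (normal data) | 84.5% | Not stated, and still not 80% |
| Rank test, efficiency 0.864 (worst case) | 80.6% | Not stated; rank tests are a fallback |

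The last row also returns the printed sample size: 25.52/0.864 = 29.5, so 30 per arm and 60 in total. It is the only reading tried that gives 60 without contradicting something the protocol states.

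**The case against.** The strongest reply is that the sentence can be read as a floor. Sixty participants do give at least 80% power for 0.8, nobody is put at a disadvantage, and enrolment need not change. The protocol also cites trials of 58 and 68 participants as informing its choice, so 60 may never have been meant as the smallest number that solves a formula. All of this stands, and it is why the point is minor. It does not make the sentence accurate, because the sentence gives a power figure and not a lower bound.

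A second reply is that the test and the metric are unnamed, so the calculation may rest on a method the reader cannot see. The worst-case rank-test calculation shows that such a method exists. This stands in part: the fault may be an unnamed method and not a slip in arithmetic. But nothing in the document says that this basis was used, and Data analysis reserves rank tests for data that remain non-normal after transformation.

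Three stronger readings are tempting and are not supported.

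- *The trial is the wrong size.* It is not. The margin is on the safe side for the stated effect and significance level.
- *The calculation is wrong because it ignores the planned ANCOVA.* Sizing by t-test and then analysing with baseline adjustment is a common conservative choice. The protocol gives no correlation between baseline and follow-up scores from which to do otherwise.
- *The hidden margin would pay for multiplicity control.* By t-test it would not keep 80% power: at 0.025 power is 78.5%, and at 0.05/6 it is 64.3%. A more favourable answer needs an assumed correlation. A split over two primary outcomes would also conflict with the Theoretical framework section, which names three primary variables (attitude, beliefs and self-efficacy). Multiplicity is a separate question and does not bear on whether the printed power is right.

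**Conclusion.** The point holds as a small reporting error. On the protocol's own inputs, 60 analysed participants give about 86% power for d = 0.8, some 6 points above the printed 80%. Equivalently, 52 would be enough for 80% power, or 60 would detect d = 0.74 at that power.

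This rests on three assumptions: 0.8 is a standardised mean difference, the comparison is a two-sample t-test, and 30 per arm are analysed. The normal approximation gives slightly different numbers (87%, 50 and 0.72) and the same conclusion. The error is conservative. The enrolment target of 80 and the dropout adjustment need no correction.

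**What to change.** Keep 80 randomised and replace the power sentence in Sampling design with wording such as:

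> With 25% loss, 60 analysed participants (30 per arm) give about 86% power for d = 0.8, or 80% power for d = 0.74, at two-sided 5% by two-sample t-test.

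If 60 came from another method, name that method and its assumptions instead, so that a reader can reproduce the figure. Either way, state that 0.8 is a standardised mean difference, if that is what is meant.

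The cost is one sentence. Enrolment, design and analysis do not change.

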#### Operational definitions

**Single session therapy.** Neff et al. [29] acknowledged that defining brief therapy is difficult and that it embodies a distinct mindset for both therapist and client, often driven by resource limitations. It could be thought of as therapy where time is allotted and treatment is rationed, emphasizing deliberate brevity over coincidental shortness. The proposed operationalization aligns precisely with the core principles of SST [2].

**Attitude towards SST.** Attitudes are described as positive or negative affective responses towards a specific psychological concept. For the BAT-Q tool [28] the attitude scale measures the attitudes of therapists towards brief therapy.

**Beliefs about SST.** Beliefs or values in the context are seen as underlying beliefs about the best way to conduct psychological interventions. For the BAT-Q tool [28] the value scale measures the perceived worth, significance, or importance placed on brief therapy by the therapists.

**Counseling self-efficacy.** Karaırmak [30] defined counseling self-efficacy as a counselor's confidence in their ability to skilfully orchestrate and utilize various techniques when working with clients in the future. The COSE-TR scale defines four factors. ‘Microskills’ factor in the COSE-TR tool operationalizes counselors' self-efficacy by assessing their confidence in adeptly utilizing various counseling techniques. The ‘Dealing with Difficult Client Behaviors’ factor evaluates counselors' self-efficacy in their fundamental knowledge, confidence in using open- or closed-ended probes, and addressing difficult client responses. ‘Cultural Competence’ measures counselors' self-efficacy in demonstrating an understanding and effectiveness in working with clients from diverse backgrounds, including their ability to relate to clients of different socioeconomic status and view situations from various cultural perspectives. The ‘Counseling Process’ factor assesses counselors' self-efficacy in guiding the therapeutic journey, including their worries about interpretation and confrontational responses, uncertainties in leading clients toward goal development, and concerns about facilitating client progress throughout the counseling relationship.

#### Measures

The quantitative data collection for both pre-test (T1) and post-test (T2) time points (before and after completing the online SST training) will utilize the same instruments BAT-Q and COSE-TR. All data will be collected online using google form.

The Beliefs and Attitudes Toward Therapy Questionnaire (BAT-Q) developed by Bolter [28], measures therapists' preferences for long-term versus short-term therapy approaches. Comprising 19 items, the BAT-Q divides into "values" and "attitudes" subscales, resulting in a total score. While the "values" subscale relies on 13 items, the "attitudes" subscale relies on the remaining six. It utilized a seven-point Likert scale and some of the items are reverse scored. A higher subscale and total score suggest higher inclination towards brief therapy. The BAT-Q established itself reliable with Cronbach alpha as 0.88 and acceptable item and test–retest reliability [29, 46]. However, its terminology requires updating for use in the context of SST. The study will adapt BAT-Q to the SST domain by replacing terms like "brief therapy" with "single-session therapy" and "patients" with "clients".

The Turkish version of Counseling Self-Estimate Inventory (COSE-TR) [30] is a shorter version of the original COSE scale [31] with 27 items designed for measuring counseling self-efficacy in collectivists culture. It demonstrates strong internal consistency, with a Cronbach's alpha coefficient of 0.90 and, the four identified factors within the scale display satisfactory reliabilities: Microskills (0.90), Dealing with difficult behaviors (0.71), Cultural competence (0.71), and Counseling process (0.79). The total score represents the overall performance by summing the scores of all individual items across all factors.

To gain a deeper understanding of the factors influencing changes in participants' attitudes, values, and self-efficacy, focus group discussions will be conducted with a purposive sample of participants who exhibit the largest and smallest pre-post test score differences. For participants with large positive score differences, the questions will focus on the specific aspects of the training program that were most helpful. For participants with large negative score differences, the questions will focus on the aspects of the training program that were less effective. The interview schedule will be validated by qualitative research experts.

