### Theoretical framework

The study is grounded in the Theory of Planned Behavior (TPB) proposed by Ajzen in 1985 [24]. The TPB posits that attitudes, subjective norms, and perceived behavioural control, closely linked to self-efficacy, predict individuals' intentions and ultimately their behavior. The training program aims to improve attitudes towards SST by highlighting its benefits and evidence-based practices. Additionally, addressing cultural norms and involving experts can reinforce subjective norms favoring SST. Finally, the design of the training and its skill-building exercises can enhance participants' perceived ability or self-efficacy to deliver effective support in a single session format. The current study measures attitude, beliefs and self efficacy as primary variables.

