### Research questions

What successful features and design elements found in the literature can be adapted to maximize engagement and learning within an online training program for mental health support in Indian cultural context?What is the level of agreement among experts on the content of each module in the web-based SST training program to be accurate and aligned with evidence-based practices in Single-Session Therapy?Does the online SST training program significantly improve mental health support providers' attitudes and beliefs towards SST compared to a waitlist control group?Does the online SST training program significantly increase mental health support providers' counseling self-efficacy in delivering SST compared to a waitlist control group?What are the experiences of participants who show the most significant and least significant changes in attitudes, beliefs and self-efficacy towards SST?

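### The protocol treats self-efficacy as one primary variable, but its reporting rule names four COSE-TR subdomains and omits the total, so no single result answers research question 4

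*Protocol article*

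**What the plan says.** Four places treat self-efficacy as one thing. Theoretical framework says "The current study measures attitude, beliefs and self efficacy as primary variables". The fourth research question asks whether the training raises "counseling self-efficacy in delivering SST compared to a waitlist control group". Expected outcomes states the hypothesis for self-efficacy as one construct beside attitudes and values. The Phase 3 Data analysis section gives the between-group model: "ANCOVA will be used to compare the post-intervention outcomes (T2) (self-efficacy, values and attitudes) between the intervention and control groups".

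Phase 3 Measures describes the 27-item COSE-TR and gives Cronbach's alpha as 0.90 for the whole scale and 0.90, 0.71, 0.71 and 0.79 for its four factors. It then defines an overall score: "The total score represents the overall performance by summing the scores of all individual items across all factors".

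Later in the same Data analysis paragraph as the ANCOVA, the reporting and significance rule reads: "All changes will be reported for attitudes, values and four subdomains of self efficacy and p values below 0.05 will be considered significant". The COSE-TR total is not in that list.

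**The concern.** Within one paragraph, self-efficacy goes from one outcome to four. Attitudes and values do not have this problem: each corresponds to one BAT-Q subscale and appears once in both sentences. Self-efficacy is the only primary variable whose unit of analysis changes.

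Research question 4 needs a yes or a no. Under the reporting rule the trial produces four p values, no total and no rule for combining them. An author could answer from the total, from any significant subdomain or from all four, and could decide after seeing the results. This is not mainly a question of alpha. Adjusting across the four subdomains would still not say which score answers the question. Nor is it a detail that an article can leave to an analysis plan, because the article does state the analysis variable, in two ways that do not agree.

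**Working it through.** **Inputs from the protocol article.** 80 enrolled, 25% dropout, 1:1 allocation, d = 0.8, two-sided 5%, 80% power (Sampling design); four COSE-TR factors (Operational definitions); p below 0.05 for each listed score (Data analysis).

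**The plan's own figure.** 60 / (1 − 0.25) = 80, so the inflation reproduces. With 30 per arm and d = 0.8, the two-sample t-test has 86% power; 80% power needs 26 per arm, or 52 in total. The stated 60 is on the safe side and does not bear on this point.

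**Assumptions, because the article does not give them.** Four subdomains of equal variance and equal weight in the total; common correlation ρ of 0.3, 0.5 or 0.7 between them; unadjusted two-sample t-tests at two-sided 5%, 30 per arm. Results are from simulation.

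**Effect sizes.** With shift δ in every subdomain, the total has mean difference 4δ and variance 4 + 12ρ, so d on the total is 2δ / √(1 + 3ρ). Setting this to 0.8 gives δ = 0.4 × √(1 + 3ρ):
- ρ = 0.3: δ = 0.55
- ρ = 0.5: δ = 0.63
- ρ = 0.7: δ = 0.70

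If one subdomain alone moves by 0.8, d on the total is 0.8 / √(4 + 12ρ), which is 0.29, 0.25 and 0.23.

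**Results** (percent of trials):

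| True effect | ρ | Total significant | Any subdomain significant | The two disagree |
|---|---|---|---|---|
| None | 0.3 | 5 | 17 | 14 |
| None | 0.5 | 5 | 16 | 11 |
| None | 0.7 | 5 | 13 | 8 |
| All four equal, d = 0.8 on total | 0.3 | 86 | 90 | 8 |
| All four equal, d = 0.8 on total | 0.5 | 86 | 92 | 7 |
| All four equal, d = 0.8 on total | 0.7 | 86 | 92 | 6 |
| One subdomain only, d = 0.8 | 0.3 | 20 | 88 | 69 |
| One subdomain only, d = 0.8 | 0.5 | 16 | 89 | 73 |
| One subdomain only, d = 0.8 | 0.7 | 14 | 90 | 76 |

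In every row most disagreements have a subdomain significant and the total not. For independent subdomains with no effect, the chance of at least one significant result is 1 − 0.95⁴ = 18.5%.

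**Sensitivity to weights.** With weights 2, 1, 0.6 and 1, the no-effect range is unchanged (8% to 14%). The one-subdomain range over the same correlations becomes 43% to 58% if the heaviest subdomain is the one that moves, and 80% to 83% if the lightest is.

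**The case against.** The strongest reply is that there is no declared conflict. The Measures sentence explains how the instrument is scored and does not call the total an endpoint. The ANCOVA sentence lists self-efficacy once, and the only overall score the article defines is the total. The later sentence can be read as added reporting detail, and leaving the total out of a list does not forbid it. This is fair as far as it goes. A reader might infer that Measures declares the total as the endpoint and that Data analysis overrules it; the text does not support that. What stands is that the favourable reading has to be supplied by the reader. The significance rule is attached to the list with four subdomains, and the ANCOVA sentence never says which COSE-TR score it uses.

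Three other inferences also fail.

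- **That the two readings give opposite answers, often.** They differ in significance, not direction. With equal effects giving d = 0.8 on the total, the four subdomains split among themselves in 72% to 35% of trials (ρ of 0.3 to 0.7). That is disagreement among subdomains, not between the total and a stated rule, and no rule requiring all four appears in the article.
- **That subdomain power falls below the sample-size figure.** Scaling d by √(0.71 / 0.90) gives 0.71 and 77% power on a t-test. But the 0.8 in Sampling design is tied to no outcome, and the planned analysis is ANCOVA. Dividing by √(1 − r²), at assumed pre-post correlations r of 0.3, 0.5 and 0.7, gives about 81%, 88% and 97%.
- **That the subdomains are all less reliable than the total.** Measures says "the four identified factors within the scale display satisfactory reliabilities", and Microskills, at 0.90, equals the whole scale.

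**Conclusion.** The point holds as an outcome left unfixed and inconsistently stated: the construct is single, an overall score is defined, and the significance rule names four other scores without saying how they answer research question 4. That rests on the text alone.

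The practical size depends on assumed correlations, weights and effect pattern. Disagreement between the total and any-subdomain readings is modest if the training moves all four subdomains together, and large if it moves only one. With no effect, counting any subdomain as success raises the false-positive rate for this question from 5% to about 13% to 17% at correlations of 0.7 to 0.3. It is a cheap improvement worth making; it does not undermine the design.

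**What to change.** In the Phase 3 Data analysis section, state that research question 4 is answered by the ANCOVA on the COSE-TR total at T2, adjusted for the T1 total. Add the total to the reporting sentence. Report the four subdomains as secondary estimates with confidence intervals that show where any change lies.

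This takes a sentence or two and no new data, because the total is the sum of items already collected, and it holds the error rate for this question at 5%. The cost is that no stand-alone significance claim can be made for a single subdomain. If the effect were confined to one subdomain, the total would be significant in only about 14% to 20% of trials on the assumptions above. If the investigators think that pattern likely, the alternative is to keep the four subdomains with a decision rule and multiplicity control stated in advance. With Bonferroni at 0.0125 each, power is about 70% per subdomain at d = 0.8 with 30 per arm on a t-test.

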#### Procedure

Participants will be recruited using personalized social media messages, targeted social media advertisements, email outreach, flyers within relevant settings, and leveraging the researchers’ professional network. Demographic data as well as their interest in completing in SST training, will be collected through a researcher-developed questionnaire. Participants who show interest in completing the SST training will be randomly allocated to either the intervention group or the control group using the research randomizer software program in 1:1 ratio. The intervention group will have access to the online training program immediately for a period of two weeks. The waitlisted control group will not have access to the online training program during the intervention period, and are offered access after post-test at the end of two weeks.

The pre-test data (T1) is collected using two scales. The first one is a modified version of the BAT-Q Scale [28] with replaced terms like "brief therapy" with "single-session therapy" and "patients" with "clients". These revisions in the item texts of the tool will undergo validation by three psychometric experts. Given that the changes are minor and primarily involve replacing terms to ensure clarity and relevance to the specific context of SST, a consensus among two experts can be considered a reliable validation. The second scale is the counselling self-efficacy scale, COSE-TR [30].

At the end of the two weeks, participants in both the intervention group and the control group will complete a post-test assessment (T2). Participants demonstrating the most significant and least significant changes in attitude and self-efficacy between T1 and T2 will be invited to two separate 30-min focus groups (top 10 and bottom 10, expecting a 50% response rate). This targeted approach facilitates the exploration of contrasting experiences. The SPIRIT Figure in Table 2 explains the schedule of enrolment, interventions, and assessments.

**Table 2 Tab2:** SPIRIT Figure for the Schedule of Enrolment, Interventions, and Assessments

Study period					
	Enrolment	Allocation	Post-allocation		Close-out
Timepoint	T_1_	0	Week 1	Week 2	T_2_
ENROLMENT					
Eligibility screen	X				
Informed consent	X				
Random Allocation		X			
INTERVENTIONS					
SST Training Group			Two weeks access to training		
Waitlist Control Group			No access to training		Two weeks access to training after assessments
ASSESSMENTS					
Quantitative					

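### The two Phase 3 focus groups are given opposite question emphases with no stated common core, so the planned comparison of themes partly reflects the interview guide

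*Protocol article*

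**What the plan says.** All references are to the protocol article; Measures, Procedure and Data analysis are those of Phase 3.

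- **Who is sampled.** Measures describes "a purposive sample of participants who exhibit the largest and smallest pre-post test score differences". Procedure plans "two separate 30-min focus groups (top 10 and bottom 10, expecting a 50% response rate", and says of the arrangement: "This targeted approach facilitates the exploration of contrasting experiences".
- **What they are asked.** Measures gives two emphases: "For participants with large positive score differences, the questions will focus on the specific aspects of the training program that were most helpful"; and "For participants with large negative score differences, the questions will focus on the aspects of the training program that were less effective". It adds: "The interview schedule will be validated by qualitative research experts". No questions common to both groups are mentioned.
- **How the answers are used.** Data analysis states: "Thematic comparisons will be drawn between participants who exhibited significant positive and negative changes in their attitudes, values, and self-efficacy". It gives the purpose as understanding what lay behind the quantitative changes, and Expected outcomes says that the focus groups will explain those changes.
- **The question served.** The fifth research question is neutral in wording: "What are the experiences of participants who show the most significant and least significant changes in attitudes, beliefs and self-efficacy towards SST".

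**The concern.** To explain score changes by comparing two groups, one must know whether a feature that one group names was also met by the other. The plan points one group towards benefit and the other towards shortcoming, and then compares what each says. The slant of the question and the membership of the group move together, so the analysis cannot tell a real difference in experience from a difference in prompting.

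At stake is the reading of the fifth research question and of the explanatory aim. A weakness of the course that both groups met could be reported as a feature of those who did badly. A strength that both groups valued could be reported as the reason why others did well. In Phase 3, moreover, the only stated route by which trainees' unfavourable experiences would be gathered is directed at one of the two groups.

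**Working it through.** There is no stated figure to reproduce. The check consists of setting the statements side by side.

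**Step 1. Question focus by type of participant (Measures).**

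| Score change | Directed to helpful aspects | Directed to less effective aspects |
|---|---|---|
| Large gain | yes | not stated |
| Large drop | not stated | yes |
| Little or no change | not stated | not stated |

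Each of the first two rows has one stated emphasis, and the two emphases are opposite. No column is filled for both groups.

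**Step 2. What the comparison can show (Data analysis).** Take two situations. In the first, a module confuses everyone. In the second, it confuses only those whose scores fell. Under the stated emphases, the group with drops is prompted for the problem in both situations, and the group with gains is prompted in neither. If participants mostly answer what they are asked, both situations give the same theme table, with confusion listed for the group with drops alone. The same holds in reverse for a feature that everyone valued. The contrast therefore cannot be taken as explaining the change unless the unprompted topic happens to come up.

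**Step 3. Who has no question focus.** The second group is sampled as having the smallest differences (Measures), or the least significant changes and the bottom 10 (Procedure). The second emphasis is written for large negative differences. A small difference is not a large negative one. Someone whose scores hardly moved fits the sampling description, yet falls in the third row of the table.

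**Step 4. Room for other topics (Procedure).** Expected attendance is 10 × 0.50 = 5 per group, so 2 × 5 = 10 people in all. A 30-minute session gives 30 / 5 = 6 minutes per person. A stated emphasis will take up much of that time, so topics outside it have limited room to surface unprompted.

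**The case against.** The strongest reply is that the article states an emphasis and no restriction. The questions are to focus on certain aspects; nothing says that other aspects are barred. The schedule is not shown and is still to be validated, and opening questions or general prompts are details that an article leaves to the full guide. A reader might infer that those who gained are asked only what helped, that those who fell are asked only what failed, and that a difference in themes is therefore guaranteed. The documents do not support that reading, and this part of the objection stands. What remains is a rule that the article does state, opposite emphases by group, followed by a comparison that it also states. Expert validation does not by itself remove this, because the experts are not asked to check that the two groups' questions are comparable.

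A second reply is that tailored follow-up is a recognised choice in sequential mixed methods, and that the fifth research question is descriptive. This also stands in part. A reader might infer that the question cannot be answered at all. That goes too far, since each group would still give relevant material on its own experience. It is the between-group comparison and its explanatory use that suffer.

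A third reply is that criticism is sought elsewhere. Phase 1 includes a group with a negative stance towards single-session work, and Phase 2 collects expert comments and ratings of user-friendliness. That is correct, so it would be wrong to say that the plan seeks unfavourable views nowhere else. Those contributors are not trial participants who have taken the finished course, however.

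**Conclusion.** The concern holds for the stated design. Question slant is tied to group, no common core is stated, and the groups are then compared. A difference in themes would arise at least in part from the guide; how large a part cannot be determined from the article. The gap for participants with little or no change is a plain mismatch between the sampling description and the question sets.

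The reach is limited: about 10 attendees, one of five research questions, and the explanatory aim under Expected outcomes. The focus groups follow the post-test, so the randomised comparison of attitudes, values and self-efficacy is untouched. The point is worth correcting but does not threaten the trial's main result.

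The conclusion rests on two assumptions: that the final schedule follows the emphases in Measures, and that participants mainly discuss what they are asked about. If the schedule already asks both groups about helpful and unhelpful aspects, the problem shrinks to a matter of wording in the article.

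**What to change.** In Phase 3 Measures, state a shared core of questions for both groups: what helped, what was less effective or unwelcome, and what the participant thinks explains the change or the lack of it. Group-specific probes can follow the core, so the tailoring is kept. The shared core also gives participants with little or no change a question focus. A fixed question order is not needed.

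In Phase 3 Data analysis, base the between-group thematic comparison on the answers to the shared questions, and report the answers to probes descriptively within each group. The expert validation could also confirm that the core is the same for both groups.

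The cost is a rewording of a schedule that is still to be validated, and less time per topic. Three core topics in 30 minutes leave at most 30 / 3 = 10 minutes each for a group of about five, and less once probes are added.
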